### Secondary outcome measures

 Duration (days) of nCPAP, need and duration of bi-level NCPAP (BiPAP) and nasal intermittent MV (N-IMV) Need and duration (days) of conventional mechanical ventilation (synchronized intermittent mandatory ventilation (SIMV), synchronized intermittent positive pressure ventilation (SIPPV), pressure support ventilation (PSV) with or without volume guarantee (VG)) or high-frequency oscillatory ventilation (HFOV) with or without VG Duration (days) of oxygen therapy and highest FiO_2_ level of oxygen concentration Duration of hospitalization Number of doses of surfactant during hospitalization Occurrence of mild, moderate, and severe bronchopulmonary dysplasia (BPD) during hospitalization. The severity of BPD is categorized according to the consensus definition [21]: treatment with oxygen >21 % for at least 28 days, plus: mild BPD: breathing room air at 36 weeks post menstrual age (PMA) or discharge, whichever comes first; moderate BPD: need for more than 30 % oxygen at 36 weeks PMA or discharge, whichever comes first; severe BPD: need for at least 30 % oxygen and/or positive pressure (PPV or nCPAP) at 36 weeks PMA or discharge, whichever comes first Time of being without any respiratory support

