### Sample size

We hypothesized that a recruitment maneuver (in HFOV modality) before surfactant administration might decrease of the need of subsequent mechanical ventilation during the first 72 h of life from 50 % [2, 5, 7] to 30 %. We calculated that 103 newborns must be enrolled in each group to detect this difference as statistically significant with 80 % power at the 0.05 alpha level using the two-sided Pearson’s chi-square test.

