### Randomisation

Infants will be allocated to one of the two treatment groups in a 1:1 ratio according to the minimization method, using an interactive web-based electronic system. Randomization will be stratified by center and gestational age (24^+0^–25^+6^ weeks or 26^+0^–27^+6^ weeks). A monthly accrual report about the study will be sent to the participating centers.

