### Primary outcome measure

The primary outcome is the need for mechanical ventilation within the first 3 days of life and, therefore, we consider IN-REC-SUR-E or IN-SUR-E a success if mechanical ventilation is not required and a failure if the infant needs mechanical ventilation in the first 72 h. Infants in both groups will be considered to have reached the primary outcome also when they are not extubated within 30 min after surfactant administration or when they meet the nCPAP failure criteria after extubation.

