### Other collected data

The following data will be recorded for each infant: gestational age (GA), birth weight (BW), sex, Apgar score at 5 min, antenatal steroid treatment, prolonged PROM of more than 18 h, diagnosis of histological and/or clinical chorioamnionitis, type of delivery, clinical risk index for babies (CRIB) II score [22], occurrence of air leaks, pulmonary hemorrhage, patent ductus arteriosus (PDA) and need for surgical closure, timing of surfactant administration, grades 3–4 intraventricular hemorrhage (IVH) [23], periventricular leukomalacia (PVL) [24], higher than grade 2 retinopathy of prematurity (ROP) [25], necrotizing enterocolitis (NEC) [26], sepsis defined as a positive blood culture or suggestive clinical and laboratory findings leading to treatment with antibiotics for at least 7 days despite the absence of a positive blood culture, length of stay in the NICU, use of systemic postnatal steroids, and mortality. The discharge from NICU will be performed when infants will not need respiratory assistance other than using oxygen therapy and central venous catheter insertion.

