### Statistical analysis

The primary efficacy analysis will be conducted on an intention-to-treat basis. An as-treated analysis will also be implemented for secondary analyses if a large number of infants do not end up getting the treatment to which they were assigned. Clinical characteristics of infants in the “IN-REC-SUR-E” and “IN-SUR-E” groups will be described using mean values and standard deviation, median value and range, or rate and percentage. Univariate statistical analysis will be performed using the Student’s *t* test for parametric continuous variables, the Wilcoxon rank-sum test for non-parametric continuous variables, and Fisher’s exact test for categorical variables. A *p* value <0.05 will be considered statistically significant. Then, treatment arm and clinical characteristics which are most likely associated with the need for mechanical ventilation (gestational age, birth weight, antenatal steroids, CRIB score) will be included in a multiple logistic regression analysis to assess their independent role in predicting the clinical outcome. Effect estimates will be expressed as odds ratios (ORs) with maximum likelihood-based 95 % confidence limits. An interim analysis will be planned when 50 infants will be enrolled in each arm. The analysis will intend to compare treatment arms with respect to efficacy, safety, futility, assessment of difficulties with patient enrollment, and, if necessary, a sample size adjustment. In the interim analysis for safety the pre-specified stopping rules are: a mortality rate more than 40 %, a rate of severe IVH more than 30 % and a pneumothorax rate of more than 10 %. The interim-analysis will be performed by an independent statistician, blinded for the treatment allocation. The statistician will report to the independent Data and Safety Monitoring Board (DSMB). The DSMB will have unblinded access to all data and will discuss the results of the interim-analysis with the Steering Committee in a joint meeting. The Steering Committee will decide on the continuation of the trial and will report to the central Ethics Committee.

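### BPD and the respiratory-support, oxygen and hospital-stay durations are defined without regard to death, so if mortality differs they can favour the arm with more deaths

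*Protocol article*

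**What the plan says.** **BPD.** The Secondary outcome measures section lists "Occurrence of mild, moderate, and severe bronchopulmonary dysplasia (BPD) during hospitalization". The definition requires at least 28 days of supplemental oxygen plus the infant's status at 36 weeks PMA, or at discharge if that is earlier. It has no category for an infant who dies before then.

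**Durations.** The same section lists days of nCPAP, BiPAP and nasal intermittent ventilation, mechanical ventilation, oxygen and hospitalisation as plain durations. It also lists time spent without any respiratory support.

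**Mortality.** It is recorded only under Other collected data, at the end of a list that closes with "use of systemic postnatal steroids, and mortality".

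**Tests.** The Statistical analysis section assigns Student's t test, "the Wilcoxon rank-sum test for non-parametric continuous variables" and Fisher's exact test. Intention to treat is stated for the primary efficacy analysis. The section also sets an interim mortality stopping rule at more than 40%.

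**Primary outcome.** The Primary outcome measure section calls the procedure "a success if mechanical ventilation is not required" and a failure if ventilation is needed within 72 h. It adds two further routes to failure: remaining intubated beyond 30 min after surfactant, and meeting the nCPAP failure criteria once extubated. Death is not named.

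**The concern.** At 24 to 27 weeks' gestation, death competes with every later respiratory outcome. For this population 36 weeks PMA falls about 8 to 12 weeks after birth (36 minus 27+6, and 36 minus 24+0). An infant who dies before 28 days cannot meet the BPD definition; one who dies later, but before assessment, cannot be graded. Death also ends ventilation, nCPAP, oxygen and hospital stay, so it reads as a short and apparently good duration.

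The Background gives improved respiratory outcome as part of the trial's purpose, and these secondary outcomes must carry that claim. If the arms differ in mortality, BPD and the durations mix respiratory benefit with loss of infants at risk. No named primary or secondary outcome would put the two together. The Background itself summarises the earlier CPAP trials by the combined risk of death or BPD, but this trial does not adopt that measure.

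**Working it through.** **The plan's own figure.** The Sample size section assumes ventilation rates of 50% vs 30%, a two-sided chi-square test at the 5% level and power of 80%. From these it concludes that "103 newborns must be enrolled in each group to detect this difference as statistically significant".

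- Uncorrected: n = [1.96·√(2·0.4·0.6) + 0.8416·√(0.5·0.5 + 0.3·0.7)]² / 0.2² = 93 per arm.
- With continuity correction: (n/4)·[1 + √(1 + 4/(0.2n))]² = 103 per arm.

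The stated 103 is reproduced with the correction. The sample size is not in dispute; it supplies n = 103 for what follows.

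**BPD.** The documents give no mortality or BPD rate by arm, so all rates here are assumptions. Let r be the BPD rate in survivors, equal in both arms, and d the proportion who die before assessment.

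- BPD per randomised infant = r(1 − d)
- Death or BPD = d + r(1 − d)

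For r = 40% and deaths of 15% vs 25%: BPD is 0.40·0.85 = 34% vs 0.40·0.75 = 30%. Death or BPD is 0.15 + 0.34 = 49% vs 0.25 + 0.30 = 55%. The range:

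| r | Deaths, A vs B | BPD per randomised, A vs B | Death or BPD, A vs B |
|---|---|---|---|
| 30% | 10% vs 20% | 27% vs 24% | 37% vs 44% |
| 50% | 10% vs 20% | 45% vs 40% | 55% vs 60% |
| 40% | 15% vs 25% | 34% vs 30% | 49% vs 55% |
| 30% | 20% vs 40% | 24% vs 18% | 44% vs 58% |
| 50% | 20% vs 40% | 40% vs 30% | 60% vs 70% |
| 30% | 20% vs 20% | 24% vs 24% | 44% vs 44% |

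In every row with unequal deaths, arm B has more deaths, looks better on BPD and is worse on death or BPD. With equal deaths there is no distortion.

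**Durations.** Assume 40 days of support in survivors and 7 days in infants who die.

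- Deaths 10% vs 20%: 40·0.9 + 7·0.1 = 36.7 days vs 40·0.8 + 7·0.2 = 33.4 days.
- Deaths 20% vs 40%: 33.4 vs 26.8 days.

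The arm with more deaths again looks better, although survivors fare identically.

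**Primary outcome.** Suppose the true rate of death or failure is 50% in both arms, and a share m of one arm dies within 72 h without meeting any failure criterion. That arm's recorded failure rate is then 50% − m. With 103 per arm, the chance of a significant result in its favour is:

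| m | Infants of 103 | Chance of a false win |
|---|---|---|
| 0 | 0 | 2.5% |
| 1% | about 1 | 3.5% |
| 2% | about 2 | 4.7% |
| 3% | about 3 | 6.3% |
| 5% | about 5 | 10.7% |

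Starting from exactly equal arms (52 failures of 103 each), 15 such deaths in one arm would be needed for Fisher's p < 0.05.

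**The case against.** **It belongs in the analysis plan.** Only a journal article is at hand. Denominators and competing-risk methods are usually set in the SAP, which is not shown. The article does not say that BPD is computed over all randomised infants, or that deaths enter as short durations. That is fair as to method, and no criticism is made of a missing method. But the outcomes are defined here, and so is the decision to keep mortality out of the primary and secondary lists.

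**A survivors-only denominator removes the gap.** In the main illustration it gives 40% vs 40%. That is correct, but it conditions on an event after randomisation and leaves the mortality difference out of the comparison.

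**The effect is small and mortality is visible.** The difference of 34% vs 30% with 103 per arm gives z = 0.04/√(2·0.32·0.68/103) ≈ 0.6, so no benefit would be declared from it. Mortality is recorded, has a stopping rule and is seen by the DSMB. This stands as a limit on the harm. A safety rule, however, does not correct the BPD and duration comparisons.

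**Stronger readings that a reader might infer.**
- That every unventilated death is a primary success. The two extra failure routes rule this out; the nCPAP failure criteria (oxygen need, acidosis, apnoea) are broad and would capture many such infants.
- That every duration favours the arm with more deaths. Time without respiratory support could be shortened by death, which works against that arm.
- That the plan expects 40% mortality. That figure is a stopping threshold, not an expected rate.

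**Conclusion.** The point holds for BPD and for days of nCPAP, BiPAP/N-IMV, mechanical ventilation, oxygen and hospital stay. As defined, these outcomes disregard death, and no primary or secondary outcome includes mortality. If mortality differs, they can favour the arm with more deaths. With an assumed 10-point mortality difference and 30% to 50% BPD in survivors, the spurious BPD advantage is 3 to 5 points, while death or BPD is 5 to 7 points worse. These figures rest on assumed rates, on equal BPD in survivors and on a denominator of all randomised infants. They show direction, not an expected bias, and the documents do not support a claim that the trial's respiratory results will be reversed.

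In the primary outcome the gap is real but narrow: it covers only deaths within 72 h after timely extubation, without ventilation and without recorded nCPAP failure. The documents give no count; that such deaths are few is a judgement. The change is worth making, but the trial's main conclusion is unlikely to turn on it.

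**What to change.** 1. List mortality as a secondary outcome.
2. Add death before 36 weeks PMA or BPD as a secondary outcome, with death and each BPD grade shown separately.
3. Report respiratory support and oxygen as days alive and free of each to 36 weeks PMA, scoring an infant who dies before then as zero. For an infant discharged earlier, status at discharge could be carried forward, in line with the BPD definition. Hospital stay can be described with deaths shown separately.
4. Add death within 72 h to the primary failure definition.

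**Cost.** This is mainly wording. Mortality, BPD and the support durations are already collected, and infants are followed to discharge or death; the case record form should be checked for the date of death. The composites must be shown with their components, so that a difference in one is not mistaken for a difference in the other. The primary event rate may rise slightly.

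### The printed BPD severity grades are neither exclusive nor exhaustive: moderate lies wholly inside severe, and infants above 21 % but below 30 % oxygen without positive pressure have no grade

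*Protocol article*

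**What the plan says.** The protocol article, Secondary outcome measures, includes "Occurrence of mild, moderate, and severe bronchopulmonary dysplasia (BPD) during hospitalization". It refers to a consensus definition (reference 21) and then prints the rules. All grades share an entry condition, oxygen above 21 % "for at least 28 days, plus" a grade-specific condition. That condition is assessed at the earlier of 36 weeks post menstrual age and discharge:

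- Mild: "mild BPD: breathing room air at 36 weeks post menstrual age (PMA) or discharge, whichever comes first". Positive pressure is not mentioned.
- Moderate: "moderate BPD: need for more than 30" per cent oxygen. There is no upper limit and no mention of positive pressure.
- Severe: "severe BPD: need for at least 30" per cent "oxygen and/or positive pressure (PPV or nCPAP) at 36 weeks PMA or discharge".

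No other section restates or corrects these cut-offs.

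**The concern.** An ordered three-level outcome needs grades that do not overlap and that together cover every infant who meets the entry condition. Here the moderate threshold sits on the same side of 30 % as the severe threshold, and nothing covers oxygen between room air and 30 % unless the infant is also on positive pressure.

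The gap concerns infants the protocol foresees. Under Other collected data, an infant may leave the NICU while still on oxygen, provided no other respiratory assistance is needed. Such an infant on, say, 25 % oxygen at the assessment point has had the required 28 days of oxygen and still needs supplementation, yet matches no grade. An infant already in room air is graded mild.

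Whoever grades or analyses this outcome would have to supply a rule that the text does not give. Dropping the ungraded infants would exclude them on a post-randomisation state. Counting them as free of BPD would rank them below infants who are better off. Staff are not blinded (Blinding section), so a grading rule that leaves room for judgement is less safe here than in a masked trial.

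**Working it through.** The plan gives no figure for this outcome, so there is none to reproduce. The check applies the printed rules to every possible state.

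**Inputs** (all from Secondary outcome measures; F is the oxygen percentage at the assessment point, P is positive pressure, yes or no; the entry condition is taken as met):

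- Mild: F = 21
- Moderate: F > 30
- Severe: F ≥ 30 or P = yes

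**Set logic.** F > 30 implies F ≥ 30, so moderate is a strict subset of severe. The region 21 < F < 30 with P = no satisfies none of the three rules. F = 21 with P = yes satisfies both mild and severe.

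**Enumeration** over whole-percent F from 21 to 100 (80 values) and both values of P (160 combinations):

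| F | P = no | P = yes |
|---|---|---|
| 21 | mild | mild and severe |
| 22–29 (8 values) | no grade | severe |
| 30 | severe | severe |
| 31–100 (70 values) | moderate and severe | moderate and severe |

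- Exactly one grade: 1 + 1 without pressure, 8 + 1 with pressure = 11
- No grade: 8
- Two grades: 70 without pressure, 1 + 70 with pressure = 141
- Moderate only: 0
- Total: 11 + 8 + 141 = 160

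**Could a tie-break rescue the text?** Taking the worst grade met removes the overlaps, but it leaves moderate empty and the gap unfilled. Taking the mildest grade met makes an infant on 25 % with nCPAP severe and an infant on 60 % with nCPAP moderate, which reverses the order.

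**Would changing only the moderate threshold be enough?** Suppose moderate becomes 21 < F < 30 and nothing else changes. The gap closes, but F = 22–29 with P = yes is now both moderate and severe (8 combinations that are severe only today). F = 21 with P = yes stays both mild and severe. Nine combinations still receive two grades.

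**Would excluding positive pressure from mild and moderate be enough?** With mild as F = 21 and P = no, moderate as 21 < F < 30 and P = no, and severe as F ≥ 30 or P = yes, the counts are 1 mild, 8 moderate and 71 + 80 = 151 severe. They sum to 160, with one grade each.

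**The case against.** The strongest reply is that the article names an external consensus definition and the printed cut-offs merely summarise it. The fault is then most plausibly a slip in a condensed text, and the full protocol or the case record form may carry a sound rule. That is a fair reason not to claim that the trial lacks a usable definition; neither the cited source nor the form is available here. It does not cure the printed text. The article chose to state the rules, and they contradict one another. If the cited definition is coherent, the article misstates it.

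Three stronger inferences are tempting, and the documents do not support them:

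- **That all oxygen levels between 21 % and 30 % are ungraded, and that only mild is clean.** Infants in that range on positive pressure are severe under the printed rule, and mild is itself ambiguous for room air on nCPAP.
- **That centres will code differently.** Local investigators do enter the data (Data collection). However, Site set-up promises written instruction on recording, and Data processing and monitoring provides for cross-checks. Inconsistent coding is a risk and has not been shown.
- **That BPD is the main respiratory secondary outcome.** The article ranks none of its secondary outcomes. BPD features in the Background rationale, while the trial hypothesis concerns the need for mechanical ventilation.

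**Conclusion.** The point stands as an internal contradiction in an operative outcome definition. As printed, the moderate grade has no members of its own. Infants above 21 % and below 30 % oxygen without positive pressure are ungraded, and room air on nCPAP falls in two grades.

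The consequence is confined to the comparison of BPD by severity, one of several secondary outcomes. The primary outcome, the sample size of 103 per group and the interim safety rules do not use the BPD grade. A reader might infer that no infant can be classified. That goes too far, since some states do receive a single grade; it is the three-level scale as a whole that fails.

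The number of infants affected cannot be derived, because the article gives no expected distribution of oxygen fraction or support mode at the assessment point. The conclusion assumes that the printed wording is what would be applied, and that positive pressure means what the severe rule lists (PPV or nCPAP).

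**What to change.** Reconcile the printed grades with the cited consensus definition so that they are exclusive and exhaustive. One wording that achieves this, subject to that check:

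- Mild: room air without positive pressure.
- Moderate: above 21 % and below 30 % oxygen without positive pressure.
- Severe: at least 30 % oxygen and/or positive pressure.

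The pressure exclusion is needed in both lower grades; altering the moderate threshold alone is not sufficient.

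Confirm that the case record form holds oxygen fraction and support mode at the earlier of 36 weeks and discharge. The article lists the highest oxygen level and durations of support, but does not name these items at that time point. Derive the grade from them by one rule for all centres, and fix that rule before the analysis. The article describes the trial as still recruiting, so when it was written this could be done in advance.

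The cost is a few words of text and one derivation rule. If the two items are already recorded, no new data are needed; otherwise one short addition to the form is required, with retrieval from clinical records for infants already past the assessment point.

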### Other collected data

The following data will be recorded for each infant: gestational age (GA), birth weight (BW), sex, Apgar score at 5 min, antenatal steroid treatment, prolonged PROM of more than 18 h, diagnosis of histological and/or clinical chorioamnionitis, type of delivery, clinical risk index for babies (CRIB) II score [22], occurrence of air leaks, pulmonary hemorrhage, patent ductus arteriosus (PDA) and need for surgical closure, timing of surfactant administration, grades 3–4 intraventricular hemorrhage (IVH) [23], periventricular leukomalacia (PVL) [24], higher than grade 2 retinopathy of prematurity (ROP) [25], necrotizing enterocolitis (NEC) [26], sepsis defined as a positive blood culture or suggestive clinical and laboratory findings leading to treatment with antibiotics for at least 7 days despite the absence of a positive blood culture, length of stay in the NICU, use of systemic postnatal steroids, and mortality. The discharge from NICU will be performed when infants will not need respiratory assistance other than using oxygen therapy and central venous catheter insertion.

### Data collection

All collected data can be obtained from the clinical records. They will be reported in electronic data sheets designed for this study. Data will be entered by the local principal investigator on a web-based electronic case record form. Access to the form will be password-protected and participants will be identified by trial number only. Clinical information will be collected at the following times:At trial entry: information on eligibility; background information and randomizationFollowing randomisation: all data above listed in “Primary outcome measure,” “Secondary outcome measure,” and “Other collected data” sections

Further information will be collected on expected serious adverse events.

In terms of the PICOT format, our study can be described as follows: P: preterm infants of 24-27 weeks failing nCPAP during the first 24 h of life; I: surfactant administered during HFOV with optimal lung volume strategy; C: surfactant administration via INSURE method using conventional positive pressure ventilation; O: need for mechanical ventilation; T: study entry until 72 h of life.

